### Data collection: use of an electronic mobile application (the app)

One of the secondary objectives of the study is to test the effectiveness of a mobile electronic data collection application (the App) in both study groups to collect real time quality data required to assess programme effectiveness and to strengthen linkage to care services. Data will be collected using the App, as well as paper-based tools developed by FPD. The App was designed for this study. The use of the App was deemed to ease the process of linkage to care as client data will be accessible on the South African Government electronic databases and could be accessed by others on the CBCT programme in real time using the Qode Insight system with which to track individual clients’ linkage to care. If a client is linked, the system will capture the name of health facility where a client is linked to care and date of linkage and initiation of care, among other details, through a password-protected online reporting portal. Clients who are lost to follow-up in the treatment cascade will be identified through the Qode Insight system. They will be tracked, and if found, counselled with the aim to reinitiate them on treatment at health facilities. In addition, data captured on the App minimises data entry challenges of accuracy and completeness. Capturing data on paper means that it must be recaptured onto the electronic database support systems (the Bulk Online Capture System or BOCS) that allows the capture of data in situations where the mobile application was not used. The use of the App is therefore expected to contribute towards the success of the entire CBCT programme. All counsellors will be trained for at least one day on using the app. The app has a minimum of 54 variables per participant while a client who tested HIV positive has at least 22 additional variables to complete and those referred for linkage to care will have at least 20 more variables to complete. The app will be completed by the counsellors who administer the interviews. The completion of the app will take place throughout the counselling and testing and linkage process. Every indicator data entry is captured directly onto the application. Participants will be interviewed in vernacular. The app has relevant skip patterns and prompts to suit participants’ various situations and ensure that all relevant questions are entered. The database is managed at FPD by a database developer. Figure 1 shows a picture of a tablet app where client data is entered.

**Fig. 1 Fig1:**
[figure not shown]
Picture showing the Mobile App data entry form designed for this study

The app will be accessible through using an assigned password to each counsellor. Each counsellor will have a user name/identity (ID) code which reflects in the database to assist programme managers to track progress per counsellor, per day. Data will be captured and saved automatically onto the app and in real-time transferred to the cloud-based database using an internet connection. In cases of limited or no internet connection, the app saves an encrypted copy of the data on the tablet/device and the counsellor then uploads the data manually, through the push of a single button, onto the database when the internet connection becomes available. Counsellors conduct manual uploads at the end of each working day to ensure all data are uploaded onto the database. After development, the App was tested and data were captured, retrieved, analysed and compared for completeness, validity and accuracy.

### Measures

HIV testing and counselling will be conducted following the South African algorithm [38]. An HIV positive status will be assessed by a first test using Alere Determine HIV-1/2 Rapid Test (Alere Medical Co. Ltd., Matsudo-Shi Chiba, Japan) which, if positive, will be confirmed by Abon HIV 1/2/0 Tri-Line Rapid Test (Abon Biopharm, Hangzhou, R. R China). In case of discordant results, final results will be confirmed by Western Blot. Data collected to facilitate linkage to care include a participant’s national ID number, age, gender, place of residence, testing place name, sub district, two telephone/mobile phone numbers, referral clinic name, and client register number. In couples testing, identifying personal data will be collected to assess discordant results. Participants will be asked if they identify themselves as belonging to any key population groups including female sex workers (FSWs), men who have sex with men (MSM), injection drug users (IDUs), and if they are clients of sex workers.

The tool also collects data on participants’ HIV testing history – if they ever tested for HIV before or they were first time testers. In terms of HIV prevention, the questionnaire asks if the participants received condoms and if they were referred for voluntary male medical circumcision, antenatal care, gender-based violence care, TB care, family planning care, antiretroviral treatment or other social services. For TB screening, a tool with six questions will be administered to assess if a participant ever, for longer than two weeks, coughed up blood in sputum, had sudden and unexplained weight loss, night sweats, fever or been in close contact with someone coughing for more than two weeks [39]. A typical question is: “Have you been coughing/coughed for longer than two weeks? Participants were requested to respond affirmatively with a “Yes” or otherwise with a “No”. To screen for sexually transmitted infections (STIs), four questions will be asked to assess if a participant ever had unprotected sex with an HIV or STI suspect, abnormal or smelly discharge or bleeding from a vagina or penis, or experienced pain during sex or when passing urine. A typical question is: “Did/Do you have an abnormal or smelly discharge from the vagina or penis?” Participants will be requested to choose yes or no as answers to the question. Female participants will be screened for pregnancy while male participants will be asked if they were circumcised. A screening tool for non-communicable diseases assesses levels of blood sugar and blood pressure.

### Ethical considerations

Written informed consent will be sought from each potential participant. In keeping with the relevant South African Law including the Children’s Act, and the South African Good Clinical Practice Guidelines (2006), all children between 12 and 17 can consent to HIV testing without consulting a parent or guardian [40, 41]. For those under 12, parental consent will be sought and when provided, assent will be sought from the child. Participants will be informed that their personal information, demographic, and testing details will be shared with health personnel at referral health facilities to facilitate linkage to care but that no additional people outside the study will be authorised to access participant data without the permission of the Principal Investigator. The benefits of participating in the study include knowing own HIV status, getting a wide range of free health screening including TB, STI, blood sugar and pressure as well as facilitated and accelerated referral to care including ART for those screening/testing positive. However, getting to know HIV status may cause one to feel anxious and/or nervous which is manageable though due to the shorter time it takes to conduct an HIV rapid test and also counselling that highlights the freely available life prolonging medicines for those testing positive. Starting ART earlier is beneficial as proved in a number of studies [42]. The study was approved by the FPD Research Ethics Committee (Protocol 13–2017) and was registered with the Pan African Clinical Trial Registry (PACTR201809873079121).

### Data analysis

Data will be downloaded from the database and retrieved in excel format through an export mechanism and exported to Stata [43] for analysis. The analysis of primary outcomes will be conducted by comparing proportions of HIV testing, positivity rates, linkage to HIV care and treatment rates, app use rates and per counsellor cost by gender and age group in the two study groups. Descriptive statistics will be performed to describe the data. Proportions stratified by age group and gender will be calculated and presented. In comparing proportions between FPD and SF, 95% confidence intervals will be calculated and presented. All analyses will be conducted using STATA 14.0. A costing analysis will be done to assess programme cost per counsellor per HIV test, positivity and linkage to care.

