## Methods

### Design

The study is a two arm non-randomised community implementation trial with a once off round of post-test follow-up per HIV positive participant to assess linkage to care. Clients will be tested by one of the HIV testing strategies – either by an existing FPD counsellor or a SF HIV counsellor under the sub-contracted model. Each study arm has 19 counsellors conducting CBCT. The overall study design is illustrated on Table 2.

**Table 2 Tab2:** Process flow for the FPD and Social Franchise HTS

Item	Activity	FPD	Social franchise
1. Counsellor Recruitment and contracting	Contract	1. Employed by FPD 2. Normal employment contract 3. Normal payroll contract 4. Work for 8 h a day	1. Unemployed, self-employed or employed elsewhere, not employed by FPD 2. Contracted by franchisee-franchisor contract 3. No restriction on hours, days worked 4. Test >/= 100 people per month 5. Test>/5 HIV + tests per month 6. Link >/= 4 HIV + clients per month
	Remuneration	1. Fixed monthly salary	1. Paid $3.20 per HIV test 2. Paid $8 per HIV + client linked
	Training	Training focussed on: 1. Pre-test, test, post-test, documentation, referral and linkage to care	Training focussed on: 1. Pre-test, test, post-test, documentation, referral and linkage to care 2. business development & management
2. Mobilisation	Community level mobilisation	Community events; flyers; campaigns (e.g. couples counselling); conducting systematic door-to-door mobilization campaigns distributing flyers, and condoms	Community events; flyers; campaigns (e.g. couples counselling); conducting systematic door-to-door mobilization campaigns distributing flyers, and condoms
	Individual level mobilisation	Informing households on the benefits and availability of testing for HIV; scheduling household level testing appointments and/or actively recruiting clients for same day HTS	Informing households on the benefits and availability of testing for HIV; scheduling household level testing appointments and/or actively recruiting clients for same day HTS

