### Sample size and sampling

Based on current rates of the CBCT programme, which were used to come up with targets for the SF model, data will be analysed after 12 months of programme implementation. Each arm will have 19 counsellors recruiting at least 100 clients per counsellor per month for 12 months excluding weekends and holidays. Requiring counsellors to test 100 clients per per month is a conservative assumption that considers SFs as new players in conducting CBCT to emphasize accuracy and quality in CBCT work. Based on this assumption and calculation, a total of 91,200 participants are expected to be recruited in 24 months and half of these (45,600) will be recruited by SFs while the other half by FPD. A 12-month follow up and a final 24 months evaluation to assess programme effectiveness will be conducted. No randomisation of counsellors or clients will be done. All sub districts were selected based on current rates of HIV infection, which is highest in the townships where predominantly black Africans reside.

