### Control arm - FPD HTS

In order to identify people infected with HIV (PLHIV) and bring them into HIV care, FPD designed and implemented a CBCT programme in 2013 that ran through 2018 [29]. The programme aimed to make significant inroads towards the UNAIDS’s 90–90-90 goal [30] through the alignment with the South African Government’s (SAGs) National Strategic Plan on HIV, STIs and TB (NSP 2012–2016) [31] and the PEPFAR/SA HIV Prevention Strategy [32]. To implement the CBCT strategy, FPD formally advertised and employed counsellors to conduct HTS. The counsellors attended a 10-day training programme covering HTS and linkage to HIV care including documentation, approaching communities, consenting as shown on Table 2. FPD managed counsellors’ daily HTS activities and remunerated them monthly without necessarily pegging the salary to HTS outputs. The client recruitment strategy for testing is described as home-based in which counsellors moved door-to-door recruiting clients in the community. FPD teams, who include a driver/counsellor and at least four other counsellors per team, drive from the office to the communities in the selected study/project sites daily to conduct HIV testing and travel back to the office. Counsellors will test and refer clients for linkage to care. Linkage to care will be confirmed by checking clinic registers and Tier.net, an electronic patient management system used for capturing patient-level data on HTS, pre-ART and ART services. Counsellors will follow up clients for up to six months to ensure that they are linked to care.

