### Intervention arm - SF HTS or SFs

In 2016, FPD CBCT introduced a separate Social franchise testing model [27] into the existing CBCT approaches (See Table 2). The programme aims at assessing effectiveness of a community-based HTS study implemented through social franchisees in Tshwane district in Gauteng province, South Africa. The model aims at providing implementation evidence by assessing success or failure of the model to inform roll out through a public-private partnership between government and non-governmental organisations. As part of the recruitment process, FPD advertised and encouraged individuals and small-scale business people, either employed or unemployed, to apply for the SF opportunity. Applicants will be interviewed by an FPD recruitment and selection panel. Successful SFs will be provided with a 10-day training on HTS, documentation, referral for ART and business management. The training on small business management is aimed at ensuring SFs obtain skills in management of mall-scale business including CBCT resources, ordering and disbursing CBCT materials and ledger balancing. Each SF (*n* = 19) will sign a contract with FPD to deliver a standards-based product of CBCT (HIV testing and linkage to care package) to decide where to conduct HIV testing daily in the designated communities, decide demographics of people to target daily, mobilise communities, families and individuals regularly, recruit clients, test them, and to link HIV positive clients to referral health facilities within the communities per agreement with clients. SFs will deliver a common brand that FPD implements and systematizes. The role of the franchisor, FPD, will be to prescribe HTS standards, recruit, train and accredit SFs, including deregistering SFs that fail to meet prescribed CBCT brand/standards. FPD will also maintain quality assurance of the SFs through making announced and unannounced visits to the SF offices and areas of work. In addition, FPD will support the SFs by establishing linkages between SFs and the referral health facilities where the SFs will refer clients for HIV prevention, care and treatment. Furthermore, FPD will facilitate access to HTS commodities and waste disposal services, verification of linkage to HIV care and treatment, access to information, education and provide communication materials for HIV prevention and marketing as well as paying SFs in accordance with numbers tested and linked to care and treatment.

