Our study design has some strengths and limitations. The strengths of the design include that it compares a new model of SFs with existing CBCT approach that has been implemented for over a decade now [14]. That the CBCT approach has been successfully implemented in at least three years offers a good standard of care to compare a new implementation programme, SF, with. The site of the implementation of the study, Tshwane district in Gauteng province, was a good selection for two main reasons. Firstly, Gauteng has an HIV prevalence similar to the national average rate. Secondly, the study sites consisted of rural, urban and peri-urban centres which is comparable to the South African population at large. In addition, the sites also contained heterogeneous populations including foreigners, local indigenous people as well as internal migrants from across other provinces. This population heterogeneity favours the generalisation of the study findings to the greater South African population for the purpose of HIV prevention through testing and treatment. Also, that the population is predominantly black African mirrors the populations that bears the brunt of the HIV pandemic in the country.

However, the fact that the two models will be implemented in the same communities (not cluster based) and that communities and clients are not randomised is a limitation for the study. Only an analysis by individual client level is possible due to non-randomisation. There may be challenges in conducting an economic analysis of costs as getting appropriate estimates of travel in the sub districts as both FPD and SFs counsellors conduct testing in the same sub-districts. On the other hand, not restricting counsellors to specific areas in the study area also enable counsellors to assess hotspots and testing in the areas of choice each day.

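### The non-randomised arms are to be compared on uptake and linkage by proportions split only by age group and gender, so a difference could reflect where and when each arm tested rather than the franchise model

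*Protocol article*

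**What the plan says.** The design and allocation are stated openly. Under Design: "The study is a two arm non-randomised community implementation trial". Under Sample size and sampling: "No randomisation of counsellors or clients will be done".

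The two arms choose their field work differently. Under Intervention arm, each SF contracts "to decide where to conduct HIV testing daily in the designated communities, decide demographics of people to target daily", and the contract's positivity target is meant to steer SFs towards hotspots. Under Control arm, "FPD managed counsellors’ daily HTS activities and remunerated them monthly without necessarily pegging the salary to HTS outputs". The Discussion adds, of counsellors in general, that "not restricting counsellors to specific areas in the study area also enable counsellors to assess hotspots and testing in the areas of choice each day".

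The Data analysis section then fixes the comparison: "The analysis of primary outcomes will be conducted by comparing proportions of HIV testing, positivity rates, linkage to HIV care and treatment rates", together with app use and counsellor cost, by gender and age group. It promises 95% confidence intervals for the comparison of the two arms. It names no further stratum, covariate, weight or matching, and no restriction to a common period.

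The Discussion concedes that shared communities and the lack of randomisation are a limitation, and says that only a client-level analysis is possible. It offers no analytic remedy. Under Measures, sub-district, testing place, referral clinic, testing history and key-population membership are all recorded. Under Follow up, the date of test is logged for HIV-positive clients.

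**The concern.** In a non-randomised comparison the analysis has to do some of the work that allocation did not. Here the protocol itself gives reasons to expect the arms to differ in where they test: one arm has daily freedom of place and clientele, and the other is managed centrally. Age group and gender cannot absorb differences between sub-districts or between months.

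For uptake and linkage such differences can pass for an effect of the franchise model. Large numbers do not help, because they narrow the interval around the biased value and leave the bias as it was. The article intends the contrast to inform roll-out, so readers need to be able to separate the contracting model from the mix of places and months.

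**Working it through.** **1. The plan's own total.** Inputs from Sample size and sampling: 2 arms, 19 counsellors per arm, 100 clients per counsellor per month, 24 months.

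2 × 19 × 100 × 24 = 91,200, or 45,600 per arm. This reproduces the stated figure. It is a recruitment projection; no effect size or power is stated.

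**2. Precision of a client-level comparison at 24 months.** The Intervention arm section gives targets of 5% positivity and 80% linkage. Independence between clients is assumed.

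- Positives per arm: 0.05 × 45,600 = 2,280.
- Linkage half-width: 1.96 × √(2 × 0.8 × 0.2 / 2,280) = 2.3 points.
- Uptake: neither the rate nor the number offered a test is given. Those offered are at least as many as those tested, so if the recruitment target is met the half-width is at most 1.96 × √(2 × 0.25 / 45,600) = 0.65 points.

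**3. Spurious difference from an unequal mix of places.** Take two kinds of place with the same linkage in both arms, so the true effect is zero. If the rates are h and l, and the arms have shares a and b in the better places, the crude difference is (a − b) × (h − l). All stratum rates and shares below are assumptions; the documents give none.

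| Linkage in the two kinds of place | Share in better places, SF v FPD | Crude difference (95% CI), points | Chance the CI excludes 0 |
|---|---|---|---|
| 85% v 75% | 55% v 45% | 1.0 (−1.3 to 3.3) | 0.13 |
| 85% v 75% | 60% v 40% | 2.0 (−0.3 to 4.3) | 0.39 |
| 90% v 70% | 60% v 40% | 4.0 (1.7 to 6.3) | 0.92 |
| 90% v 70% | 70% v 30% | 8.0 (5.7 to 10.3) | about 1 |

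Third row in full: SF 0.6 × 90 + 0.4 × 70 = 82%; FPD 0.4 × 90 + 0.6 × 70 = 78%; difference 4 points.

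**4. Does stratifying remove it?** For the third row, a Mantel-Haenszel risk difference over the two strata is 0.0, as it must be when the stratifier is the source of the imbalance.

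**5. Positivity.** With assumed positivity of 8% and 3% and the same 60/40 v 40/60 mix, the crude rates are 6.0% and 5.0%, a difference of 1.0 point (0.7 to 1.3). This case is different in kind: finding high-yield places is what the SF contract asks for, so the difference is partly the intended effect.

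**The case against.** The strongest reply has four parts.

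- **The article is condensed.** It never calls the analysis unadjusted, and covariate lists usually sit in an analysis plan. It is true that the lack of adjustment is inferred. But the section does fix the primary comparison and name its splits, and the limitation it concedes is left without a remedy.
- **Targeting is mechanism.** Choice of place and clientele is a contract term, and the Discussion expects the model to reach first-time testers and key populations. First-time testing is a secondary outcome, and FPD builds the links between SFs and referral facilities. This stands. It rules out place adjustment as the main analysis of positivity. It also argues against putting referral clinic, testing history or key-population status in the main linkage model.
- **The arms share communities, mobilisation methods and the linkage process.** Counsellors in both are to offer testing to each available person at the homes they visit. This limits differences in place but does not remove them.
- **Covariates for those who decline may not exist.** The interview follows signed consent, so the documents show no individual data on refusers. This stands and restricts what can be done for uptake.

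A reader might also infer more than the text supports:

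- **Different referral clinics.** Not stated. Clients name a preferred clinic and counsellors visit all referral clinics in the area.
- **Different working hours.** SFs have no restriction on hours and FPD staff work eight hours a day. That permits a difference without establishing one, and recruitment in each arm is counted without weekends and holidays.
- **Control data from 2013 onwards.** "FPD designed and implemented a CBCT programme in 2013 that ran through 2018" dates the programme, not the study data. The SF model began in 2016, but equal arms and equal durations are planned within the existing programme. What is missing is only a sentence tying the comparison to common months.
- **Both arms choosing whom to test.** Choice of clientele is explicit only for SFs.

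**Conclusion.** The point holds for uptake and linkage. The planned comparison, split only by age group and gender, cannot separate the franchise model from where and when each arm tested.

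The size of the resulting bias is unknown. Under the assumed scenarios it runs from 1 to 8 points for linkage, against a client-level half-width of 2.3 points. At the mild end the interval would usually still include zero; at the 4-point case it would usually exclude it. These figures rest on assumed stratum rates and shares, on the contract targets of 5% and 80%, and on independence between clients. They show that the problem can matter, not that it will. The direction of any bias is not determined by the documents.

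For positivity the crude comparison is a legitimate measure of yield and should remain. The change is worth making before analysis, but it does not invalidate the design.

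**What to change.** In Data analysis:

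1. State the estimand: the total programme effect, or the effect at like places and times, for each primary outcome.
2. **Linkage.** Make the main estimate a risk difference, adjusted or standardised for age, sex, sub-district and calendar month, with standard errors clustered on counsellor. This remains a client-level analysis, as the Discussion requires.
3. **Uptake.** Do the same with only those variables known for everyone offered a test, for example sub-district and month if offers are logged that way.
4. **Positivity.** Keep the crude rate as the yield estimate, with a version adjusted for sub-district and month as secondary.
5. State that only calendar months in which both arms were testing are compared.
6. Put adjustment for referral clinic, first-time-tester status and key-population status in a sensitivity analysis, because these may be part of how the SF model works.
7. Show crude results alongside throughout.

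The cost is analysis wording and modest extra programming. Sub-district, age and sex are already recorded for tested clients, and the test date is logged for HIV-positive clients, so linkage needs no new data. Uptake depends on how offers are logged. Intervals will be wider, and adjusting for sub-district may take out a small part of the intended targeting effect, which is why the crude results stay in view.
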